### Efficacy

2.7

We anticipate that combining tDCS with the intervention will amplify its impact on the outcome measures and improve the durability of the treatment-induced gains.

### Safety

2.8

The stimulation parameters used in this study are not expected to pose any significant risks. A systematic review examining the adverse effects of tDCS across all published studies, including those involving vulnerable populations, found that side effects like tingling and itching under the electrodes were mild and resolved quickly after stimulation. No serious adverse effects have been reported to date. Therefore, it can be concluded that tDCS, when applied within the specified parameters, is a safe intervention.

### Sample size

2.9

Based on the previous investigations conducted by Karsan et al. and Moien et al. [25,26], and employing G∗Power software [47], it is determined that 31 subjects per group (totaling 62 participants overall) are required to detect a statistically significant difference regarding a time × group interaction via a two-way mixed model analysis of variance (ANOVA). The time variable is designated as the within-subject factor (i.e., before the intervention and immediately, six weeks, and 3 months following the intervention), while the group is classified as the between-subject factor (i.e., anodal or sham tDCS). The dependent variable examined is the percentage of stuttered syllables (SS%). Type I (α) and type II (β) error rates are set at 0.05 and 0.20, respectively, with an effect size of 0.17.

### Statistical analysis

2.10

Descriptive statistics will be calculated for demographic and baseline characteristics, in addition to primary and secondary outcomes for all participants engaged in the study. For each participant, summary statistics including mean, standard deviation, median, minimum, and maximum values will be documented for quantitative variables. Frequency tables will be employed to present the data of qualitative variables. Differences among demographic variables will be assessed using Student's t-tests for quantitative variables and chi-square tests for qualitative variables. To evaluate the effect of tDCS on the primary and secondary outcome measures, mixed-model ANOVAs will be used, with group (anodal vs. sham) as the between-subjects factor and time (baseline, immediately post-treatment, 6 weeks, and 3 months) as the within-subjects factor.

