#### Primary outcome measures

2.4.1

In this research, the average scores of the percentage of Stuttered Syllables (%SS) obtained from a 10-min unscheduled telephone call will serve as the primary outcome measure. A baseline assessment will be collected one week before the intervention. The identical assessment will be conducted immediately after, and six weeks and three months following the last intervention session (post-treatment assessments). A 10-min unscheduled telephone call with each participant will be conducted by individuals other than the researcher, and this call will be recorded using a call recorder application. Two experienced specialist raters, blinded to the treatment conditions and assessment time points, will independently evaluate and calculate the %SS of all speech samples. The recordings will be coded and screened to ensure anonymity. To calculate the %SS, the total number of syllables associated with unambiguous stuttering for each recorded sample will be counted, divided by the total number of syllables for that sample, and then multiplied by 100 [42]. Stuttering will be characterized as occurrences that involve either (i) repetitions of phonemes, words, or phrases, (ii) prolonged phonemes, or (iii) blocks. It will be important to highlight that, per Riley's definition of stuttering (1994), interjections, silent blocks, and repetitions of whole words or phrases will be considered stuttering if they are articulated abnormally and with tension. Otherwise, they will not meet the criteria for stuttering [43]. The expected mean %SS score at the three post-intervention time points in the anodal tDCS group will be hypothesized to be significantly lower than that found in the sham tDCS group (a diminished %SS score will indicate a less severe form of stuttering). Additionally, no significant difference will be expected between groups at the baseline time point.

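### The four-level ANOVA models baseline %SS as an outcome rather than a covariate, which wastes precision on the primary comparison

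*Protocol article*

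**What the plan says.** Section 2.10 assigns the primary and secondary outcomes to mixed-model ANOVAs "with group (anodal vs. sham) as the between-subjects factor and time (baseline, immediately post-treatment, 6 weeks, and 3 months) as the within-subjects factor". Section 2.9 sizes the trial on the time-by-group interaction of a two-way mixed ANOVA, with time levels "before the intervention and immediately, six weeks, and 3 months following the intervention". It concludes that "31 subjects per group (totaling 62 participants overall) are required", and gives the inputs as follows: "Type I (α) and type II (β) error rates are set at 0.05 and 0.20, respectively, with an effect size of 0.17". Baseline is thus an outcome level both in the analysis and in the sizing, and the article mentions no baseline covariate.

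Section 2.4.1 hypothesises lower mean %SS under anodal stimulation at the three post-intervention times and adds: "Additionally, no significant difference will be expected between groups at the baseline time point". Sections 2.1 and 2.3.2 fix the order of events: the baseline call precedes speech therapy, and allocation comes later, at the practice stage.

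**The concern.** Because allocation follows the baseline call, the arms can differ on baseline %SS only by chance. Baseline therefore carries no information about the treatment effect as an outcome, but it does carry information as a predictor of later %SS. In the four-level ANOVA, the interaction compares the arms on how the later visits depart from baseline. It is in effect an analysis of changes, so the full baseline variance enters the error. A covariate would remove only the part of the post-treatment variation that baseline predicts.

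At stake is power that could be had from data already being collected. The choice of test within the ANOVA matters too. The interaction spends 3 degrees of freedom on any pattern over time, although the hypothesis is a shift in one direction at all post-treatment visits. The group main effect averages baseline in and so dilutes a constant post-treatment effect to three quarters.

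**Working it through.** **Inputs.** From section 2.9: 31 per arm, N = 62, alpha 0.05, power 0.80, effect size 0.17 (read as Cohen's f; the metric is not named), k = 2 groups, m = 4 times. The article gives no SD of %SS and no correlation between visits, so these are assumptions and are varied below. Effects are in units of the post-treatment SD.

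**1. The plan's own figure.** For the within-between interaction, lambda = f² × N × m / (1 − rho), on 3 and 3(N − 2) df.
- rho 0.36 and sphericity: 0.0289 × 62 × 4 / 0.64 = 11.2, power 0.80, so N = 62 results.
- rho 0.5 and sphericity: lambda = 14.3, power 0.90 at N = 62; N = 50 would be enough.
- rho 0.5 and epsilon 0.75: N = 60.

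So 62 is attainable. It cannot be verified, because neither rho nor epsilon is stated.

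**2. What f = 0.17 means.** Take a constant difference d at the three post-treatment visits and none at baseline. The group differences depart from their average by −0.75d once and +0.25d three times. Then f² = (1/4) × (0.5625 + 3 × 0.0625)/4 × d² = 0.046875 d², so f = 0.2165 d, and f = 0.17 corresponds to d = 0.785 SD.

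**3. Variance, adjusted against change score** (equal SDs of 1, common rho).
- One visit: (1 − rho²)/(2 − 2 rho) = (1 + rho)/2, which is 0.65, 0.75 and 0.85 at rho 0.3, 0.5 and 0.7.
- Mean of three visits, with V = (1 + 2 rho)/3: adjusted V − rho²; change V + 1 − 2 rho. At rho 0.5 this is 0.417/0.667 = 0.625; at rho 0.36 it is 0.52.

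**4. Detectable effect at 80% power, 31 per arm, rho 0.5.**
- 3-df interaction: the required lambda on 3 and 180 df is 11.14. Solving 0.046875 d² × 62 × 4 / 0.5 = 23.25 d² = 11.14 gives d = 0.69 SD.
- 1-df change contrast: 2.80 × √(2 × 0.667/31) = 0.58 SD (0.59 with the t distribution).
- Baseline-adjusted mean: 2.80 × √(2 × 0.417/31) = 0.46 SD.

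The step from 0.69 to 0.58 comes from replacing a 3-df test by a 1-df contrast. The step from 0.58 to 0.46 comes from the covariate.

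**5. Baseline more variable than post-treatment.** With baseline SD twice the post-treatment SD and rho 0.5, the change variance is 0.667 + 4 − 2 = 2.667, the adjusted variance is still 0.417, and the ratio is 0.16. Simulated power for a constant effect of 0.5 post-treatment SD (20,000 trials per scenario, 31 per arm):

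| Baseline/post SD ratio | Interaction, uncorrected | 1-df change | Baseline-adjusted |
|---|---|---|---|
| 1 | 0.49 | 0.66 | 0.85 |
| 2 | 0.26 (0.21 with Greenhouse-Geisser) | 0.22 | 0.84 |

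**6. Type I error of the interaction F**, nominal 0.05, over assumed correlations of 0.3 to 0.7 with baseline and 0.5 to 0.8 among post-treatment visits:

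| Baseline/post SD ratio | Uncorrected F |
|---|---|
| 1 | 0.052–0.066 |
| 1.5 | 0.056–0.078 |
| 2 | 0.071–0.090 |
| 3 | 0.091–0.101 |

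With Greenhouse-Geisser the rate is 0.046–0.051 throughout, with baseline still a level. The change contrast (0.047–0.052) and the adjusted analysis (0.047–0.053) hold their level without correction.

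**The case against.** The strongest defence is that analysis and sizing agree. The test powered in 2.9 is one that 2.10 can deliver, and at the stated effect size it reaches 0.80 to 0.90 power for rho between 0.36 and 0.5. With randomised arms and an ordinary sphericity correction, the interaction test is valid. This stands: the point concerns efficiency, not a contradiction.

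The SDs and correlations above are assumptions, which also stands. The direction of the loss depends on them less than its size does: with equal SDs and a common correlation, adjustment gains at every rho below 1. A larger baseline SD is plausible, because entry requires moderate-to-severe stuttering and both arms must then reach a severity rating below 2 in clinic tasks before stimulation. The article gives no variance to confirm it.

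Three stronger readings are tempting, and the document does not support them:
- A reader might infer that using baseline as a level inflates the type I error. It does not. Inflation comes from non-sphericity in an uncorrected F and disappears with an epsilon correction. The article neither plans nor excludes one, and such detail may sit in an analysis plan not shown.
- A reader might infer that participants who miss a visit are dropped. No missing-data rule or method of fitting is stated.
- A reader might credit the whole gap from 0.69 to 0.46 SD to baseline handling. About half of it comes from the degrees of freedom.

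**Conclusion.** The point holds as one of precision. Sections 2.9 and 2.10 fix baseline %SS as a fourth outcome level, although it precedes allocation and the hypothesis lies at the three later visits. With equal SDs, rho 0.5 and 31 per arm, the covariate alone lowers the detectable effect from about 0.58 to about 0.46 SD, and a single-df contrast accounts for the drop from 0.69 to 0.58. The loss is larger if baseline %SS is more variable than post-treatment %SS. A type I error of about 5% to 10%, over assumed SD ratios of 1 to 3, is only a conditional risk: it arises if the F test is left uncorrected. The planned analysis is avoidably inefficient rather than wrong, and the change is worth making because it is nearly free.

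**What to change.** In 2.10, analyse the three post-treatment visits for %SS (and severity rating) in a repeated-measures model with group, visit, group-by-visit, baseline and baseline-by-visit. Name the group difference averaged over the post-treatment visits as the primary contrast; without that, the 0.46 SD figure does not apply. In 2.9, state that 62 was derived for the less efficient interaction test.

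If the four-level ANOVA is kept, state a Greenhouse-Geisser correction and name either the group-by-time interaction or the post-minus-baseline contrast as the primary test, not the group main effect. The correction protects the error rate but recovers no power.

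The cost is revised wording in both sections. No new data or participants are needed.

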### Randomization

2.5

This study is a randomized, double-blind, sham-controlled trial, where participants will be randomly assigned to either the intervention group or the control group. The random allocation of participants will help prevent selection bias and ensure a balanced distribution of confounding factors between the study groups. For the randomization process, blocked randomization will be employed. Specifically, one of the six blocks used in this study (ABAB, BABA, AABB, BBAA, BAAB, ABBA) will be randomly selected. A will represent the intervention group, and B will represent the control group. Each participant will be assigned an ID number and allocated to one of the treatment groups. The individual who generates the random allocation will not be involved in any other phase of the trial.

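### Entering baseline %SS as a level of the time factor ties the tDCS effect to raw change from baseline, which is valid but less precise than adjusting for baseline

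*Protocol article*

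**What the plan says.** Section 2.10 names one efficacy model for the primary and secondary outcomes: "mixed-model ANOVAs will be used, with group (anodal vs. sham) as the between-subjects factor". The repeated-measures part of that model is specified as "time (baseline, immediately post-treatment, 6 weeks, and 3 months) as the within-subjects factor". Baseline is thus one of four outcome levels.

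Section 2.9 uses the same structure. The within-subject levels are "before the intervention and immediately, six weeks, and 3 months following the intervention", the target is the time-by-group interaction, and "31 subjects per group (totaling 62 participants overall) are required". The other inputs are given as "Type I (α) and type II (β) error rates are set at 0.05 and 0.20, respectively, with an effect size of 0.17".

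Section 2.4.1 (Primary outcome measures) expects lower mean %SS under anodal tDCS at all three post-intervention time points, and adds that "no significant difference will be expected between groups at the baseline time point". The article mentions neither a baseline covariate nor a constraint that the two groups share one baseline mean.

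**The concern.** In a group-by-time interaction where baseline is one of the times, the treatment effect at a post visit is (post minus baseline, anodal) minus (post minus baseline, sham). Baseline is subtracted with weight 1, whatever its real relation to the later values. If the true regression slope of post on baseline is below 1, too much is subtracted. Baseline noise is then added to the estimate, and an arm that starts worse by chance appears to improve more.

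The design gives some reason to expect a slope below 1. Baseline %SS is taken before any speech therapy (2.1). Both arms then complete the establishment stage (2.3.1) before stimulation, so raw change also contains each person's response to that stage, which is unrelated to tDCS. %SS on an unscheduled call is also the measure that determines eligibility (2.1), so some regression to the mean is likely.

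Precision is at stake in a trial of 62 people, as is the sensitivity of the estimate to a chance baseline difference. Since %SS is collected before treatment anyway, the adjustment costs nothing in data.

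**Working it through.** **Inputs from section 2.9:** 31 per group, 4 time points, alpha 0.05, power 0.80, effect size 0.17 (read as Cohen's f). **Assumptions, none stated in the article:** correlation rho among repeated %SS values, equal SDs (set to 1), compound symmetry, epsilon 1, no dropout.

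**1. The plan's own N.** For the within-between interaction, lambda = f² × N × m / (1 − rho).
- At rho 0.36: 0.0289 × 62 × 4 / 0.64 = 11.2. With df 3 and 180, power is 0.80, so N = 62 is reproduced.
- Rho 0.36 is not the only route. Rho 0.5 with epsilon 1 gives N = 50, rho 0.5 with epsilon 0.7 gives 62, and 50/0.8 = 62.5 (63 after rounding up) would correspond to 20% dropout. The correlation behind 62 therefore cannot be recovered from the article.

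**2. Effect implied by f = 0.17.** For a sustained pattern (0 at baseline, d at each post visit), f² = 3d²/64, so d = 0.17/√(3/64) = 0.785 SD.

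**3. Per-person variance for the mean of the three post visits.**
- Raw change: (1 + 2rho)/3 + 1 − 2rho = (4 − 4rho)/3.
- Adjusted for baseline: (1 + 2rho)/3 − rho².
- Ratio, adjusted to raw: (1 + 3rho)/4.

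| rho | raw change | adjusted | ratio |
|---|---|---|---|
| 0.36 | 0.853 | 0.444 | 0.52 |
| 0.37 | 0.840 | 0.443 | 0.53 |
| 0.5 | 0.667 | 0.417 | 0.625 |
| 0.7 | 0.400 | 0.310 | 0.775 |
| 0.9 | 0.133 | 0.123 | 0.925 |

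**4. Like-for-like power, both tests 1 df.** For the same averaged contrast with d = 0.785 SD and 31 per arm, raw change against adjusted gives 0.91 against 0.995 at rho 0.37, and 0.96 against 0.997 at rho 0.5.

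**5. Leakage of a chance gap.** Given a baseline difference g, the expected raw-change estimate is d + rho × g − g = d − (1 − rho)g. With 31 per arm, the standard error of the baseline difference is √(2/31) = 0.254 SD. At rho 0.36, a gap of one standard error shifts the estimate by 0.64 × 0.254 = 0.163 SD, and 0.163/0.785 is about a fifth of the planned effect.

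**6. Unequal SDs.** At a single visit, the variance that raw change adds over adjustment is (SD_base − rho × SD_post)². It grows as baseline becomes more variable and vanishes only when the slope is 1. If baseline SD were twice the post SD (assumption) at rho 0.36, raw change would be 1 + 4 − 2 × 0.36 × 2 = 3.56 and adjusted 1 − 0.36² = 0.870, so raw change would have about 4.1 times the adjusted variance.

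**7. Joint 3-df tests.** Simulated power (8,000 trials per row, 31 per arm, d = 0.785 SD, equal SDs):

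| baseline-post / post-post correlation | planned interaction | adjusted, 3 df | adjusted average, 1 df |
|---|---|---|---|
| 0.36 / 0.36 | 0.80 | 0.97 | 0.995 |
| 0.5 / 0.7 | 0.91 | 0.93 | 0.98 |
| 0.5 / 0.8 | 0.92 | 0.90 | 0.97 |
| 0.6 / 0.8 | 0.96 | 0.95 | 0.99 |

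When post visits correlate more with each other than with baseline, the 3-df advantage shrinks, disappears or slightly reverses. The adjusted single contrast remains ahead, but part of that lead comes from using 1 df instead of 3.

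**The case against.** The strongest reply is that nothing here is an error. Under randomisation the planned interaction is unbiased on average and, with sphericity handled, keeps its type I error. Sections 2.9 and 2.10 describe the same model, so the sample size and analysis agree. All of this stands. A reader might infer that the analysis is invalid or that the trial is underpowered for its own test. The article supports neither inference.

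A reader might also infer that the estimate carries chance imbalance in full. It does not: baseline is subtracted, and only (1 − rho) of the gap remains, with reversed sign.

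The size of the loss is uncertain. Rho 0.36 is back-solved, and other unstated inputs reach about 62 equally well. A larger baseline SD is plausible but undocumented. The severity criterion for leaving the establishment stage (2.3.1) concerns tasks with the clinician in the clinic, not an unscheduled call, and restricting entry to moderate-to-severe stuttering truncates baseline, which works the other way. So the fourfold variance figure shows only what would follow if that assumption held.

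The Randomization section's statement that allocation will help prevent selection bias and "ensure a balanced distribution of confounding factors between the study groups" might be read as a guarantee of balance. The verb help can govern both clauses, so nothing needs correcting there.

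Finally, a separate analysis plan may contain adjusted or sensitivity analyses. It could add to section 2.10, but that section already fixes where baseline enters the efficacy model. The point is therefore about a stated choice, not an omission.

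**Conclusion.** The point holds as a recommendation on precision. As written, baseline enters the tDCS comparison with a slope fixed at 1, and for any named contrast adjustment is at least as precise, apart from the small cost of estimating the slope. With equal SDs and a common correlation, the variance of the averaged post-treatment contrast would fall by 48% at rho 0.36, 37.5% at 0.5, 22.5% at 0.7 and 7.5% at 0.9. The saving is larger if baseline is more variable than the post values.

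The direction is secure whenever the slope is not 1. The size is not, because the article gives neither rho nor any SD. The advantage belongs to a named contrast and cannot be promised for a joint 3-df test.

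**What to change.** **Section 2.10.** Take the three post-treatment %SS values as the outcome, with group, visit, group-by-visit, baseline %SS and baseline-by-visit in the model. An equivalent longitudinal model that keeps baseline as an outcome but constrains the two groups to a common baseline mean would serve as well. Name the baseline-adjusted anodal-minus-sham difference as the treatment contrast, for example averaged over the three post visits, which matches the sustained effect expected in 2.4.1. Do the same for SR and speech naturalness. Analyse OASES at 3 months with baseline OASES as covariate, since 2.4.2.3 schedules it only before the intervention and at 3 months.

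**Section 2.9.** Keep N = 62. State that it was derived from the unadjusted four-level interaction, give the correlation assumed, and say that it is expected to be conservative for the adjusted contrast. Without this, 2.9 would describe a test that 2.10 no longer runs.

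**Section 2.5.** No change is needed.

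**Cost.** A few sentences in two sections, with no new visits, measurements or participants. The change should be fixed before unblinding.

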### Ethical approval al and consent to participate

2.11

This study will adhere to ethical principles as well as national norms and standards for conducting medical research in Iran (approval ID: IR.TUMS.MEDECINE.REC.1402.318, September 5, 2023, Research Ethics Committees of the School of Medicine, Tehran University of Medical Sciences). Furthermore, the ethics committee will review and approve the informed consent form. Before initiating any aspect of the study, the principal investigator will secure written informed consent from all participants.

### Consent for publication

2.12

The researchers will have the freedom to use the study results for educational and scientific purposes, but written approval from the study sponsor will be obtained before submitting the manuscript.

### Availability of data and materials

2.13

All information about participants will be kept confidential and will not be made available to the general public. Additionally, every document, data set, audio recording, and other materials will be assigned a unique participant identification number for coding, ensuring that the participants' identities remain confidential. To ensure confidentiality, the names of the subjects will not be disclosed, and all related materials will be coded with participant identification numbers. The data sets utilized and assessed during the study will be obtainable from the corresponding author upon making a reasonable request.

## Discussion

3

This study is a randomized controlled trial with follow-up assessments to evaluate the effectiveness of combining tDCS with fluency shaping intervention to enhance speech fluency in adults who stutter. The primary outcome measure to assess the treatment's impact will be the percentage of syllables stuttered (SS%). The intervention's effects will be monitored for up to 3 months to rule out any short-lived improvements with limited clinical relevance. The results of this study will provide valuable insights into the effectiveness of tDCS as a supplementary treatment for reducing the percentage of syllables stuttered (SS%) and its long-term stability over an extended period.

In this study, we will stimulate the IFG while the person performs various tasks such as reading, monologues, dialogues with the clinician, dialogues with strangers, and telephone conversations with friends and strangers. This approach considers findings that individuals with stuttering face greater challenges in maintaining fluency during complex conversational tasks [[31], [32], [33]]. Furthermore, we will assess the effect of stuttering on an individual's quality of life using the OASES questionnaire. This tool provides a thorough evaluation of stuttering's impact, measuring its influence on various life circumstances and the individual's overall well-being [45]. In conclusion, we expect this study to demonstrate that combining tDCS with fluency shaping intervention will have a supplementary effect on stuttering. This effect is likely to involve not only a reduction in SS% but also improvements in the overall quality of life for adults who stutter.

